## VII - 5 - STUDY TERMINATION

The sponsor may decide to terminate the whole study early due to:

- insufficient recruitment;
- unresolved technical issues;
- express desire of the investigators;
- repeated and unjustified protocol violations.

# VIII – QUALITY CONTROL AND ASSURANCE

The research will be conducted in accordance with the standard operating procedures of the Clinical Research Unit (URC) / AP-HP.

The performance of the study at the research sites and the treatment of subjects will be done in accordance with the Declaration of Helsinki and the Good Clinical Practice guidelines in force.

## VIII - 1 - MONITORING PROCEDURES

The CRAs representing the sponsor will carry out visits to the research sites according to the follow-up schedule for patients in the protocol, the enrolments at the various research sites and the level of risk assigned to the research study. The research has a risk level A.

- Start-up visit at each site: before enrolment, for implementation of the protocol and familiarisation with the various parties involved in the biomedical research study.

- At the next visits, the case report forms will be reviewed as the research progresses by the CRAs. The principal investigator at each site, as well as the other investigators who enrol or undertake follow-up with individuals participating in the research, agree to receive visits from the CRAs at regular intervals.

In accordance with the Good Clinical Practice guidelines, the following items will be reviewed at the site visits:

- Compliance with the protocol and procedures set out for the research;
- Verification of the patient informed consent forms;
- Examination of the source documents and comparison with the data reported in the case report form in terms of accuracy, missing data, and consistency of the data according to the regulations set out by the procedures of the URC / AP-HP ?

- Closure visit: biomedical research documents, archiving.

## VIII - 2 – TRANSCRIPTION OF INFORMATION INTO THE CASE REPORT FORM

The research data will be collected using the CleanWEB electronic case report form. The data will be centralised in a server located at the Operational Services Department (DSO) of AP-HP, [name].

An initial version of the eCRF may be put online and tested after sending the specific study specifications by fax to the company TELEMEDICINE. Once the Coordinator, the Head of Project, the Clinical Research Unit (URC), the Data Manager and the Statistician have agreed on the final version of the eCRF, and following the release of the appropriations, and submission of the purchase order to the company TELEMEDICINE, the eCRF will come into operation.

In accordance with the Good Clinical Practice guidelines, the case report form on which the research data are transcribed must correspond to at least the following standard presentation:

- At the start of the form, the following are normally included: the title of the research study, the patient’s study reference, possibly the contact information of the individual taking part in the research (no more than three letters of their surname or the first initials of their surname and first name), randomisation number (where applicable), and inclusion and exclusion criteria in the form of a check-list, which allows subject selection to be validated with respect to the study population. At the end of the research, when the research database has been “frozen”, the eCRFs of each patient will be printed and signed by the investigator. The references of the research and of the person taking part in the research will then appear in the form of a slip on each page to allow data to be identified in all cases.
- The visit and/or sampling dates of the data transcribed must be reported in this eCRF as well as the time of the research to which they correspond.
- Results of the doses must contain the units of measurement, and even the laboratory standards in the event that these vary with the technique used.
- The following items must be included at the end of the eCRF:

- Concomitant treatments;

- Non-serious adverse events (AEs);

- End of study/Early termination;

- Outside planning, an SAE form.

All the information required by the protocol must be provided in the case report form and an explanation must be provided by the investigator for any missing information.

Information must be transferred to the case report forms as soon as it becomes available, whether clinical or paraclinical information.

Incorrect information detected in the case report forms will be replaced in the form by a registered investigator, who will log in to the software with his or her access information (user name and password). These codes are strictly personal and confidential, and under no circumstances may be passed on to third parties. They help ensure data confidentiality and authenticate the interventions. Access information is associated with an electronic signature system which validates the data entered by the investigator. Each signature is stamped with the date and time and recorded in the research Audit Trail. Signed information cannot be changed. However, the investigator may void his or her signature if he or she wishes to correct any information. Voiding a signature is also subject to stamping with the date and time.

Subject anonymity will be guaranteed by mentioning no more than the research study number, the initials of the surname and first name of the individual taking part in the research in all documents required for the study, or by erasing any personal information using a suitable method (e.g., correction fluid) from the source documents to be included in the research documentation.

The electronic data file will be declared to the CNIL in accordance with the appropriate procedure for the case.

# IX – STATISTICAL DATA MANAGEMENT

The statistical analysis will be ensured by the [name] Epidemiology Centre.

## IX -1- PLANNED STATISTICAL METHODS

The statistical analysis will be carried out independently by a blinded statistician from the Clinical Epidemiology Centre, using Statistical Analysis System version 9.1, under the responsibility of [name] and [name]. A Statistical Analysis Plan will be prepared and validated prior to the freezing of the database and the unblinding. The Statistical Analysis Plan may be revised during the study, in order to take into account any changes made to the protocol or any changes in the performance of the study which have an impact on the originally planned statistical analyses. All versions will be kept in the study file.

## IX -1- 1- Descriptive statistics

The distribution of the parameters will be summarised according to the nature of the variable studied for the whole population and by group.

The descriptive statistics for each of the criteria will be expressed by the following parameters:

For quantitative data: sample size, mean, standard deviation of the variable, standard deviation of the mean, median, first and third quartiles, minimum, maximum and number of missing pieces of data. The 95% confidence interval of the mean will also be described.

For qualitative data: sample size and percentage associated with each of the classes. The 95% confidence interval of the percentage will also be described.

## IX -1- 2- Baseline criteria

For the criteria reported at the screening and/or enrolment visit, a descriptive analysis will be carried out on both groups. The qualitative variables will be described by their sample size, percentage and data missing by response method, and the quantitative variables will be described by their sample size, mean and standard deviation. In the event of quantitative variables with asymmetrical behaviour, these will be presented with their median and interquartile range (25th percentile; 75th percentile). No statistical tests comparing the treatment groups derived from the randomisation will be performed.

## IX -1- 3- Early withdrawals from the study

Subjects withdrawing from the study early and the reason for this will also undergo a descriptive analysis by group and for the total population.

## IX -1- 4- Compliance and duration of the study

The patient follow-up parameters will be analysed for each treatment group and for the total population: total follow-up duration, compliance.

## IX -1- 5- Primary endpoint analysis

An intention-to-treat analysis will be carried out, i.e., all patients randomised will be analysed in their randomisation arm, regardless of the treatment received and any missing information. The bilateral tests will be carried out at the 5% threshold. The return-to-work rate percentage will be compared using the Chi-squared test.

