# SUMMARY

| **Title** | Effectiveness of a Short, Intensive and Standardised Spa Therapy for Subacute and Chronic Low Back Pain on Return to Work for Patients in Sick Leave From 4 to 24 Weeks Duration |
| --- | --- |
| **Principal Investigator** | [name] (Hôpital Cochin) |
| **Recruiting sites** | Hôpital Cochin AP-HP Paris, Hôpital Nord CHU Clermont-Ferrand, Hôpital Lapeyronie CHU Montpellier, CHU Nancy, Etablissements thermaux d’Aix les Bains et Dax |
| **Spa centres** | Saint Amand les eaux, Royat, Balaruc les Bains, Amnéville les Thermes, Aix les bains et Dax. |
| **Study duration** | 36 months (24-month enrolment period) |
| **Patient follow-up** | 12 months |
| **Study aim** | Primary objective:  To evaluate the efficacy of a short, standardised spa therapy intervention on the return-to-work rates at 1 year for patients on sick leave due to lower back pain from 4 to 24 weeks’ duration.  Secondary objectives:  To evaluate the efficacy of a short, standardised spa therapy intervention on the pain, function, quality of life and number of days of sick leave at 1 year for patients on sick leave due to lower back pain from 4 to 24 weeks’ duration. |
| **Methodology** | A multi-centre, comparative, randomised, pragmatic trial using a modified ZELEN method. |
| **Number of sites** | 6 recruiting sites and 6 spa centres |
| **Number of patients** | 700, of whom:  - 350 in the intervention arm (standardised spa treatment)  - and 350 in the control arm (standard treatment) |
| **Selection criteria** | Inclusion criteria:   - Men or women aged from 18 to 60 years (inclusive); - Isolated lower back pain or back and radicular pain after classification of the disease (with the lower back numeric pain scale score being higher than the radicular numeric pain scale score); - Patients on sick leave due to common lower back pain from 4 to 24 weeks’ duration and for those in which an extended period of sick leave is expected; - Medical examination carried out in advance, the results of which will be communicated to the patient; - Patients having provided their written informed consent to take part in the study; - Patients affiliated with a social security scheme (beneficiary or entitled).   Exclusion criteria:   - Cognitive or behavioural difficulties making the assessment impossible; - Difficulties in comprehension and communication in the French language, making the assessment impossible; - Contraindication to undergo a short spa therapy programme. |

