# I - INTRODUCTION

## I - 1 - DATA FROM THE LITERATURE

Disability and sick leave related to lower back pain represent a major public health problem in developed countries (Andersson GB, Lancet 1999) and their costs to the healthcare system are comparable to those of heart disease, diabetes and depression (Druss BG, Am J Psychiatr 2000). The longer the sick leave lasts, the less likely it is that the patient will return to work (Waddell G, Occupational Medicine 2001). Extended periods of sick leave can reflect the level of complaints and functional incapacity, but being on sick leave could be an independent risk factor of extended sick leave. Factors such as professional experiences considered to be negative, low level of confidence in capacity to return to work and a low level of self-esteem have been identified as barriers for returning to work in this clinical situation (Magnuson L, Disab Rehabil 2007). Aside from the financial benefits, returning to work may also be a therapeutic improvement factor for lower back pain.

The rate of transition from acute lower back pain to chronic form is currently the subject of debate, as recent studies appear to contradict the previously stated rates of 8% to 10% with persistent pain as reported at 1 year in 47% in an Australian study (Menezes L, BMJ 2009) and 14% at 3 months in a French study (Coudeyre E, PloS ONE 2007). Subacute lower back pain (lasting between 4 and 12 weeks), however, is recognised as a preferred therapeutic target for preventing the transition to chronic form and the consequences this would have in terms of disability and treatment costs (Savigny P, BMJ 2009). Various interventions, which are often multidisciplinary, have shown an interest in reducing the intensity of the symptoms in this situation, but a significant number of patients have delayed symptoms and are on sick leave (Anema JR, Spine 2007).

Only one study has reported the progress of patients suffering from subacute lower back pain in France (Poiraudeau S, Rheumatol 2006). Around half of the patients were still symptomatic at 3 months, 41% of them had resorted to sick leave lasting an average of 30 days, and 20% had extended periods of sick leave. The non-return-to-work factors in subacute lower back pain have not been widely studied. A recent Norwegian study reported that the pain intensity at rest and at work and negative expectations related to return to work were non-return factors (Reme SE, BMC Musculoskeletal Dis 2009).

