## III - 3 – RANDOMISATION ARM ASSIGNMENT

Randomisation will be stratified by site. The randomisation list will be prepared with variable block sizes. The list and block size will not be communicated to the investigators. The secrecy of the assignment will be upheld using a computerised randomisation system.

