## IV - 3 - REQUIRED NUMBER OF SUBJECTS

The return-to-work rate at 1 year is estimated to be 70% in the control group. The hypothesis is to reach 80% in the intervention group. With a 5% risk and a power of 80%, a total of 600 patients are planned to be enrolled: 300 patients in the short spa therapy group and 300 patients in the control group. Taking into account the risk of loss-to-follow-up, 700 patients will be enrolled.

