## IX -1- 6- Secondary analyses

A linear mixed effects regression model will be used to compare the variations between the groups of the quantitative secondary endpoints (number of days of sick leave, number of periods of sick leave, pain, Quebec scale, MOS SF-12, HAD, FABQ and CSQ). The variable to be studied will therefore be the difference between the randomisation value (D0) and that of interest (1 year), as well as the difference between the randomisation visit and those of the interim visits (3 months and 6 months). The difference in the Δ between the groups will be modelled with the following fixed effects: the group variable (2 modalities), the enrolment value as a quantitative covariate (centred variable), the visit variable (3 modalities) and the interaction between the time and the visit, allowing us to estimate the treatment effect at each visit. The model will therefore allow us to compare the adjusted means (to the baseline value and the values of the interim visits) of the variations between the final visit and the enrolment visit (as well as between the interim visits and the enrolment visit). A random effect on the patient will be added to this model in order to take into account the correlation induced by the repetition of the measurements performed in the same patient. This linear mixed model for repeated measurements (MMRM) allows the assessments performed at each visit to be taken into account, as well as the randomly missing data (the model will also integrate the endpoint values at the different visits, enrolment variables which are potentially predictive of the missing data). The area under the curve of pain between enrolment and 1 year, assessed every week, will be calculated using the trapezoidal rule and compared using the non-parametric Mann–Whitney U test. The Q-TWIST will be calculated from the percentage of time spent by a patient in various states (percentage of time spent in inactivity, time spent with acceptable pain (less than 3 on a scale from 0 to 10 which corresponds to the PASS), time spent with pain greater than 3). The values assigned to these states will be defined at the time of the blind review of the data. The means will be compared using the non-parametric Mann–Whitney U test.

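### Randomisation is stratified by site, but site and recorded prognostic values are left out of the primary and Mann–Whitney comparisons: a modest efficiency loss, not an error

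*Protocol*

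**What the plan says.** Section III-3 states: "Randomisation will be stratified by site". The Summary counts "6 recruiting sites and 6 spa centres".

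For the primary endpoint, section IX-1-5 states: "The return-to-work rate percentage will be compared using the Chi-squared test". The Summary names the same test. No stratification factor or covariate is attached to it. On error rate, the section adds: "The bilateral tests will be carried out at the 5% threshold".

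In section IX-1-6, the AUC of pain "will be calculated using the trapezoidal rule and compared using the non-parametric Mann–Whitney U test", and TWIST is also compared by Mann–Whitney. The other quantitative secondary endpoints go into a linear mixed model. Its listed fixed effects include group, visit and the enrolment value of the endpoint, but not site.

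The introduction (section I-1) says: "The longer the sick leave lasts, the less likely it is that the patient will return to work". Eligibility admits patients with 4 to 24 weeks of leave (section IV-1). Section VII-1 records the start date of leave and pain on a 0 to 100 scale at D0.

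The planning assumptions in section IV-3 are: "The return-to-work rate at 1 year is estimated to be 70% in the control group" and "The hypothesis is to reach 80% in the intervention group".

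**The concern.** If a stratification factor predicts outcome, stratified randomisation balances it between arms. A test that ignores the factor then uses a standard error that is slightly too large: it stays valid but becomes conservative, and some of the benefit of stratifying is lost. Leaving out a prognostic baseline variable that has been recorded also costs power.

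Both conditions are plausible here. Recruitment routes differ by region (employees of one company in Auvergne only), and two sites enrol through an independent assessor rather than a hospital department, so return-to-work rates may differ by site. The protocol itself says that sick-leave duration matters, and the eligible range is wide. For pain, the plan is uneven within one section: endpoints in the mixed model are adjusted for their enrolment value, while AUC pain is not adjusted for D0 pain.

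At stake is precision in a trial planned at about 80% power, whose protocol names recruitment as a main difficulty.

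**Working it through.** **1. The plan's own figure.** Inputs from section IV-3: 70% v 80%, two-sided 5%, power 80%, 1:1 allocation. With pooled variance:

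n per arm = [1.960 × √(2 × 0.75 × 0.25) + 0.842 × √(0.70 × 0.30 + 0.80 × 0.20)]² / 0.10² = (1.200 + 0.512)² / 0.01, which gives 294 after rounding up.

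The total is 588, against 600 planned. Power at 300 per arm is Φ[(0.10 × √300 − 1.200) / 0.608] = Φ(0.874) = 80.9%. The planned size is therefore consistent with the Chi-squared test.

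**2. Analytic effect of adjustment.** If site and covariates explain a share R² of the outcome variance, the effective n per arm is about 300/(1 − R²). The documents do not give R², so a range is assumed.

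| Assumed R² | Power at 300 per arm | n per arm for 80% power |
|---|---|---|
| 0% | 80.9% | 294 |
| 2% | 81.7% | 289 |
| 5% | 82.9% | 280 |
| 10% | 84.8% | 265 |
| 20% | 88.7% | 236 |

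Site alone is likely to sit near the top of the table. A between-site SD of 5 percentage points around 75% gives R² = 0.05² / (0.75 × 0.25) = 1.3%; an SD of 10 points gives 5.3%.

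**3. Simulation with a generic covariate.** 600 evaluable patients, six equal sites, 1:1 within site, 3,000 trials per scenario. Assumed: site SD on the logit scale, and log odds ratio per SD of one baseline covariate. CMH is the Cochran–Mantel–Haenszel test by site. The logistic model has site, plus the covariate where there is one.

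| Site SD | Covariate log-OR | Power: Chi-squared | Power: CMH | Power: logistic | Type I error: Chi-squared |
|---|---|---|---|---|---|
| 0 | none | 81.2% | 81.2% | 81.3% | 5.1% |
| 0.3 | none | 81.2% | 81.4% | 81.6% | 4.4% |
| 0.5 | none | 81.5% | 82.8% | 82.9% | 4.4% |
| 0.8 | none | 82.2% | 85.0% | 85.1% | 3.7% |
| 0.3 | 0.5 | 80.8% | 81.0% | 82.8% | 4.7% |
| 0.5 | 0.5 | 82.9% | 84.3% | 85.6% | 4.7% |
| 0.5 | 1.0 | 80.5% | 81.4% | 86.4% | 4.5% |

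Type I error for CMH and logistic regression was 4.8% to 5.3%. Simulation error is about 0.7 points on power and 0.4 on type I error. A site SD of 0.8 is large: one SD either side of 70% is roughly 51% to 84%.

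**4. Simulation with weeks of sick leave as the covariate.** 5,000 trials per scenario, same layout, with assumed site rates and an assumed odds ratio per extra week of prior leave.

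| Site rates | OR per week | Chi-squared | CMH | Logistic (site + weeks) |
|---|---|---|---|---|
| 58% to 82% | 0.94 | 80.4% | 81.2% | 82.3% |
| 58% to 82% | 0.90 | 81.2% | 81.8% | 84.0% |
| 66% to 74% | 0.94 | 80.7% | 80.8% | 81.5% |
| 66% to 74% | 0.90 | 79.8% | 79.9% | 81.6% |

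Null rejection was 4.4% to 5.5% throughout.

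**5. Reading the results.** Site alone adds 0.0 (81.2 to 81.2) to 2.9 points (82.17 to 85.03 before rounding). Site plus a covariate adds 0.8 (80.7 to 81.5) to 5.8 points (80.53 to 86.37 before rounding). No scenario lost power.

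**6. AUC pain.** With baseline correlation ρ, ANCOVA multiplies the variance of a difference in means by 1 − ρ²: 0.84 at an assumed ρ of 0.4, and 0.64 at 0.6. The planned test is Mann–Whitney, not a difference in means. Its relative efficiency depends on the distribution of AUC, which the protocol does not describe. The direction of the gain is clear; its size against the planned test is not.

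**The case against.** The strongest reply is that nothing here is wrong. An unadjusted Chi-squared test after stratified 1:1 randomisation is valid, needs no model, compares directly the two rates named as the endpoint, and matches the sample size. A statistical analysis plan is promised in section IX-1 and could add adjusted supporting analyses. This stands as to validity. It does not remove the point, because the protocol names the unadjusted test as primary; an adjusted primary analysis in a later plan would depart from it.

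Second, the gains are small and depend on assumed effects. An odds ratio of 0.94 to 0.90 per week means that the odds fall to 0.94²⁰ = 0.29 or 0.90²⁰ = 0.12 of their starting value over the 20-week eligible span. The introduction supports the direction, not that strength. This stands: with no site or covariate effect, the gain is about zero.

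Third, the power figures assume 600 evaluable patients, whereas section IX-3 sets missing outcomes to failure in the tested arm and success in the reference arm. If 50 of 350 were missing per arm (an assumption), the planning rates would become 240/350 = 68.6% v 260/350 = 74.3%, reversing the effect. This also stands: the figures do not describe the analysis with that imputation, and covariate adjustment would not repair it.

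Fourth, a reader might infer that D0 pain is discarded. The AUC runs from enrolment, so D0 pain plausibly forms its first point, and visit pain is adjusted for its enrolment value in the mixed model. What is missing is D0 pain as a covariate for the AUC.

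**Conclusion.** The point holds as an efficiency improvement. Site is the randomisation stratum and is not named in any comparison; weeks of leave at enrolment are unused for the primary endpoint; D0 pain is not a covariate for AUC pain. Under the assumed effects and 600 evaluable patients, adjusting for site is worth about 0 to 3 points of power, and site plus a prognostic covariate about 1 to 6. In the scenarios with a covariate, most of the gain usually comes from the covariate rather than from site.

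Three stronger readings are not supported:

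- **The primary test is invalid or inflates alpha.** Under the assumed site effects of step 3 its type I error was 3.7% to 4.7%, so it is at most slightly conservative; the null results in step 4 straddle 5%.
- **The trial is too small for its test.** The planned 600 exceeds the 588 required.
- **A set number of patients is lost on AUC pain.** The 1 − ρ² factor has a different comparator, and ρ is assumed, so no patient-equivalent figure should be quoted against Mann–Whitney.

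Nor is the crude test without merit: it is simple and directly marginal. A standardised risk difference keeps the marginal reading while using the baseline data.

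**What to change.** In section IX-1-5 and the Summary, make the primary analysis a comparison adjusted for site and weeks of sick leave at enrolment: logistic regression with arm, site and weeks, reported as a standardised risk difference with its 95% confidence interval. At minimum, use a Cochran–Mantel–Haenszel test stratified by site. Keep the crude Chi-squared test as a supporting analysis.

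In section IX-1-6, analyse AUC pain by rank ANCOVA with D0 pain and site, compare TWIST by the van Elteren test stratified by site, and add site as a fixed effect in the mixed models.

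Name the covariates before unblinding, so that their choice cannot be questioned later. The cost is a few words in three places. The variables are already collected, and the sample size need not change.
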